### **3.3.6      Pharmacokinetic evaluations**

The pharmacokinetics of PRO051 (AUC,  $C_{\max}$ ,  $C_{\text{trough}}$ ,  $t_{\max}$ , clearance, volume of distribution and elimination half-life) will be evaluated.

Plasma samples for these evaluations will be collected at visits as shown in Appendix 2.

## **4      Subject selection**

### **4.1      Subject population**

Twelve to eighteen male patients aged at least 5 and not older than 16 years on the first day of drug administration with Duchenne muscular dystrophy resulting from an exon deletion correctable by treatment with PRO051.

### **4.2      Inclusion criteria**

1. Boys aged between 5 and 16 years inclusive.
2. Duchenne muscular dystrophy resulting from a mutation correctable by treatment with PRO051.
3. Not ventilator dependent.
4. Life expectancy of at least 6 months.
5. No previous treatment with investigational medicinal treatment within 6 months prior to the study.
6. Willing and able to adhere to the study visit schedule and other protocol requirements.
7. Written informed consent signed (by parent(s)/legal guardian and/or the patient, according to the local regulations).

### **4.3      Exclusion criteria**

1. Aberrant RNA splicing and/or aberrant response to PRO051, detected by *in vitro* PRO051 assay during screening.
2. Known presence of dystrophin in  $\geq 5\%$  of fibers in a pre-study diagnostic muscle biopsy.
3. Severe muscle abnormalities defined as increased signal intensity in  $>50\%$  of the tibialis anterior muscle at MRI.
4. FEV1 and/or FVC  $< 60\%$  of predicted.
5. Current or history of liver or renal disease.
6. Acute illness within 4 weeks prior to treatment (Day 1) which may interfere with the measurements.
7. Severe mental retardation which in the opinion of the investigator prohibits participation in this study.
8. Severe cardiac myopathy which in the opinion of the investigator prohibits participation in this study.
9. Need for mechanical ventilation.
10. Creatinine concentration above 1.5 times the upper limit of normal (age corrected).
11. Serum ASAT and/or ALAT concentration(s) which suggest hepatic impairment.
12. Use of anticoagulants, antithrombotics or antiplatelet agents.
13. Subject has donated blood less than 90 days before the start of the study.
14. Current or history of drug and/or alcohol abuse.
15. Participation in another trial with an investigational product.

### **4.4      Concomitant medication/therapies**

Anticoagulants, antithrombotics and antiplatelet agents are not allowed during the study. Other concomitant medication including glucocorticosteroids is allowed. However, if possible medication usage should not change during the study. Medication (including OTC medication, homeopathic remedies and herbal preparations) used and changes in the use of medication should be carefully recorded in the CRF.

Glucocorticosteroid use should be stable for at least 2 months prior to enrolment, and should be kept constant during the study unless medical reasons dictate otherwise.

## **4.5 Subject withdrawal criteria**

A withdrawal is a subject who stops prematurely (for any reason).

In case a serious adverse event related to the study medication occurs, the subject must be withdrawn, unless doing so would harm the subject in the opinion of the investigator.

In case study medication is discontinued (for any reason), the subject may be withdrawn from the study.

If, during the course of the study, there is deterioration in the subject's wellbeing or the investigator feels that it is in the subject's best interest to be withdrawn from the study, the subject can be withdrawn.

The subject has the right to withdraw from the study at any time and for any reason, without affecting his future management and treatment. Reasons for subject withdrawal will be documented on the CRF.

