### **5.6.8 Laboratory Safety Parameter Stopping and Follow-up Criteria**

#### **5.6.8.1 Hepatic Toxicity**

Laboratory safety assessments including liver chemistries will be performed at selected visits, refer to Tables 6 - 14 in Appendix 2 for exact time points.

- ALAT  $\geq 8x$  ULN and total bilirubin  $2x$  ULN (plus  $>35\%$  'direct' bilirubin) or ALAT  $\geq 8x$  ULN and INR  $>1.5$ .
- $\gamma$ -GT  $>2x$  ULN and bilirubin  $2x$  ULN (plus  $>35\%$  'direct' bilirubin) or  $\gamma$ -GT  $>2x$  ULN and INR  $>1.5$

If a subject's results meet either of these criteria, the tests should be repeated immediately. If the results still meet these criteria, the study medication should be stopped until such time that the Sponsor (in discussion with the Investigator) considers that the benefit of further treatment with PRO051 outweighs the risk to the individual subject.

NOTE: if serum bilirubin fractionation is not immediately available, study medication should be discontinued if ALAT  $\geq 8x$  ULN and total bilirubin  $\geq 2x$  ULN. Serum bilirubin fractionation should be performed if testing is available. If testing is unavailable, record presence of detectable urinary bilirubin on dipstick, indicating direct bilirubin elevations and suggesting liver injury.

- ALAT  $\geq 8x$  ULN associated with symptoms of hepatitis (e.g. onset or worsening of nausea, anorexia, jaundice or abdominal pain) or hypersensitivity (fever, rash, eosinophilia).

If a subject's results meet this criterion, the test should be repeated immediately alongside a discussion with the Medical Monitor. Depending on the result of the re-test and general clinical picture, appropriate action with regards to discontinuing study medication will be decided between the Sponsor and Investigator.

Given the progressive and fatal nature of this disease, it is felt important that the hepatic stopping criteria allow the flexibility for the potential to re-start dosing in this subject population following an individual subject benefit: risk assessment.

However, if a subject's results meet the criterion below, the tests should be repeated immediately. If the results still meet this criterion, the study drug should be permanently stopped.

ALT  $>2x$  baseline values and bilirubin  $2x$  ULN (plus  $>35\%$  'direct' bilirubin) or ALT  $>2x$  baseline values and INR  $>1.5$ .

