Standard liver follow-up will be implemented following repeat testing confirmation of any of liver findings as described above. If a subject's results meet any of these criteria the following processes should be completed:

- Report the event to Prosensa within 24 hours of learning of its occurrence;

- Complete the appropriate case report form (CRF) and SAE data collection tool. Note: all events mentioned above must be reported as an SAE.;
- Complete the liver imaging and/or liver biopsy CRFs if these tests are performed;
- Make every reasonable attempt to have subjects return to clinic within 24 hours for repeat liver chemistries, liver event follow up assessments (see below), and close monitoring;
- A specialist or hepatology consultation is recommended;
- Monitor subjects twice weekly until liver chemistries (ALAT, ASAT, alkaline phosphatase, bilirubin) resolve, stabilize or return to within baseline values.

In addition, make every attempt to carry out the liver event follow up assessments described below:

- Viral hepatitis serology including:
  - Hepatitis A immunoglobulin M (IgM) antibody;
  - Hepatitis B surface antigen and Hepatitis B Core Antibody (IgM);
  - Hepatitis C RNA;
  - Cytomegalovirus IgM antibody;
  - Epstein-Barr viral capsid antigen IgM antibody (or if unavailable, obtain heterophile antibody or monospot testing);
  - Hepatitis E IgM antibody;
- Serum creatine kinase (CK), glutamate dehydrogenase (GLDH) and lactate dehydrogenase (LDH);
- Fractionate bilirubin, if total bilirubin  $\geq 2x$  ULN;
- Obtain complete blood count with differential to assess eosinophilia;
- Collect blood sample for measurement of drug concentration within one month of last dose. Record the date/time of this blood sample draw and the date/time of the last dose of study medication prior to blood sample draw on the CRF. If the date/time of the last dose is unclear, provide the subject's best approximation. If the date/time of the last dose cannot be approximated OR a PK sample cannot be collected in the time period indicated above, do not obtain a PK sample. Instructions for sample handling and shipping are provided in the SPM;
- Record the appearance or worsening of clinical symptoms of hepatitis or hypersensitivity, such as fatigue, nausea, vomiting, right upper quadrant pain or tenderness, fever rash or eosinophilia as relevant on the AE report form;

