#### **6.4            Discontinuation of study medication**

In case the study medication is stopped for any reason, the Investigator will discuss the reasons with the Sponsor and a decision will be made as to whether the subject is withdrawn from the study or receives further treatment with PRO051 following an individual subject risk: benefit assessment.

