#### **7.1.2      Serious Adverse Events**

A serious adverse event is any untoward medical occurrence that, at any dose:

a. Results in death

b. Is life-threatening

NOTE: The term 'life-threatening' in the definition of 'serious' refers to an event in which the subject was at risk of death at the time of the event. It does not refer to an event, which hypothetically might have caused death, if it were more severe.

c. Requires hospitalization or prolongation of existing hospitalization

NOTE: In general, hospitalization signifies that the subject has been detained (usually involving at least an overnight stay) at the hospital or emergency ward for observation and/or treatment that would not have been appropriate in the physician's office or out-patient setting. Complications that occur during hospitalization are AEs. If a complication prolongs hospitalization or fulfills any other serious criteria, the event is serious. When in doubt as to whether "hospitalization" occurred or was necessary, the AE should be considered serious. Hospitalization for elective treatment of a pre-existing condition that did not worsen from baseline is not considered an AE.

d. Results in disability/incapacity, or

NOTE: The term disability means a substantial disruption of a person's ability to conduct normal life functions. This definition is not intended to include experiences of relatively minor medical significance such as uncomplicated headache, nausea, vomiting, diarrhea, influenza, and accidental trauma (e.g. sprained ankle) which may interfere or prevent everyday life functions but do not constitute a substantial disruption.

e. Is a congenital anomaly/birth defect

f. Medical or scientific judgement should be exercised in deciding whether reporting is appropriate in other situations, such as important medical events that may not be immediately life-threatening or result in death or hospitalization but may jeopardize the subject or may require medical or surgical intervention to prevent one of the other outcomes listed in the above definition. These should also be considered serious. Examples of such events are invasive or malignant cancers, intensive treatment in an emergency room or at home for allergic bronchospasm, blood dyscrasias or convulsions that do not result in hospitalization, or development of drug dependency or drug abuse.

g. All events of possible drug-induced liver injury as stated in section 5.6.8.1

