Medical and scientific judgment should be exercised in deciding whether expedited reporting is appropriate in other situations, such as important medical events that may not be immediately life-threatening or result in death or hospitalization but may jeopardize the subject or may require intervention to prevent one of the other outcomes listed in the definition above. These should also be considered serious.

A death occurring during the study or which comes to the attention of the investigator within 30 days of study drug administration, whether considered treatment related or not, must be reported.

In the event of an SAE the investigator may immediately stop treatment if it is considered in the best interest of the subject. In case a serious adverse event related to the study medication occurs, the subject must be withdrawn, unless doing so would harm the subject in the opinion of the investigator.

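### In the extension, a drug-related hepatic SAE under three of the four hepatic criteria falls under both a withdraw-unless-harmful rule and a rule that allows restart on benefit-risk, with no stated precedence

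*Protocol*

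**What the plan says.** **Withdrawal rule.** Protocol section 4.5 states: "In case a serious adverse event related to the study medication occurs, the subject must be withdrawn, unless doing so would harm the subject". The exception is the investigator's to judge. Section 7.1.2 repeats the rule: "the subject must be withdrawn, unless doing so would harm the subject in the opinion of the investigator". The sentence in 4.5 stands ahead of both 4.5.1 (study period) and 4.5.2 (treatment beyond the study period), so it covers the extension. The same section makes withdrawal optional, not required, when drug is merely discontinued.

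**SAE status of hepatic events.** Section 5.6.8.1 says of its hepatic findings that "all events mentioned above must be reported as an SAE". Item g of the SAE definition in 7.1.2 agrees: "All events of possible drug-induced liver injury as stated in section 5.6.8.1".

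**Hepatic rule.** Section 5.6.8.1 has four criteria. For the first two, once confirmed on repeat testing, "the study medication should be stopped until such time that the Sponsor (in discussion with the Investigator) considers that the benefit of further treatment" outweighs the risk. For ALAT with symptoms, action on discontinuing is settled between sponsor and investigator after a re-test. The section says that room to restart is intended. It then sets a fourth criterion apart, ALT above twice baseline with bilirubin or INR, for which a confirmed result means a permanent stop.

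**Rule after any stop.** Under 6.4, once drug is stopped for whatever reason, investigator and sponsor discuss it and "a decision will be made as to whether the subject is withdrawn from the study or receives further treatment with PRO051", on an individual risk-benefit assessment.

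**The concern.** The same clinical event can be reached by two instructions that start from different places. One makes leaving the study the default and allows a single exception. The other makes a treatment hold (or, for ALAT with symptoms, a case-by-case decision) the default and keeps dosing possible. They ask different questions: would withdrawal harm this boy, or does further treatment offer more benefit than risk? They also name different decision makers.

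What is at stake is first a safety matter: whether a boy with a drug-related liver event leaves the study or may be dosed again could depend on which section a site reads. Safety and tolerability is a stated objective (section 2), and 5.6.5.1 gives hepatic monitoring the highest importance. There is also a data consequence. A withdrawn boy has the final visit in 4.5.2 and then leaves, while a boy on hold stays in scheduled assessment and may gain further exposure. The discontinuation counts in the accountability summary (8.5.5.2) would then partly reflect a site's reading of the protocol.

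**Working it through.** No arithmetic applies: the protocol gives no figure on this point. The check sets the four sections side by side.

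1. **Where the overlap can arise.** Section 5.6.8.1 belongs to 5.6, safety during treatment beyond the study period. The dose-escalation part is not affected.

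2. **Which events enter the withdrawal rule.** SAE status is automatic for the hepatic events, but 4.5 applies only to SAEs related to study medication. Causality is the investigator's judgement (7.2.1.2). A hepatic event judged unrelated is an SAE and raises no conflict.

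3. **Criterion by criterion, for a confirmed event judged related:**

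| Criterion in 5.6.8.1 | Action in 5.6.8.1 | Who decides there | Action in 4.5 and 7.1.2 | Conflict when the harm exception does not apply |
|---|---|---|---|---|
| ALAT with bilirubin or INR | Stop; resumption possible on benefit-risk | Sponsor, in discussion with investigator | Withdraw | Yes |
| Gamma-GT with bilirubin or INR | Stop; resumption possible on benefit-risk | Sponsor, in discussion with investigator | Withdraw | Yes |
| ALAT with symptoms | Depends on re-test and clinical picture | Sponsor and investigator together | Withdraw | Yes |
| ALT against baseline, with bilirubin or INR | Permanent stop | Fixed by the rule | Withdraw | Not with 4.5, but with 6.4 (step 6) |

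4. **The two branches of the exception.** If the investigator believes withdrawal would harm the boy, 4.5 lets him stay and 5.6.8.1 can then run its course, so there is no contradiction. If the investigator does not believe this, 4.5 requires withdrawal, while 5.6.8.1 holds the boy pending a benefit-risk decision and 6.4 still lists further treatment as an outcome. Withdrawing closes the option that 5.6.8.1 deliberately keeps open; holding departs from the mandatory wording of 4.5.

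5. **Precedence.** None of 4.5, 5.6.8.1, 6.4 or 7.1.2 says which governs. Section 7.1.2 contains both the item that points to 5.6.8.1 and the mandatory-withdrawal sentence, with no carve-out between them.

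6. **Section 6.4 against the permanent stop.** Section 6.4 covers a stop for any reason and includes further treatment among its outcomes. The fourth hepatic criterion excludes further treatment. This mismatch does not depend on relatedness or on the harm exception.

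**The case against.** The strongest defence is that the rules can be read cumulatively: stop drug; withdraw unless the harm exception applies; if it does apply, resume only when the benefit-risk condition in 5.6.8.1 is also met. Section 5.6.8.1 permits resumption and never compels it, and it governs drug while 4.5 governs the subject. On that reading no site is forced to break one rule to obey another. This stands in part. A reader might infer that a site can never comply with both sections; the text does not support that, because under the harm exception they fit together. But the cumulative reading is nowhere stated. Where the exception does not apply, it removes the restart flexibility that 5.6.8.1 says is important, and it overrides the open choice in 6.4.

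A second defence is that the specific hepatic section overrides the general one. That is a reasonable drafting convention, but the protocol does not adopt it, and 7.1.2 repeats the general rule just after citing 5.6.8.1.

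A third is that withdrawal simply means stopping drug. The protocol separates the two acts: 4.5 makes withdrawal optional after drug is discontinued, and 5.6.5.10 lists stopping drug and withdrawing the subject as distinct steps.

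A fourth point stands in full. The investigator controls both entry to the 4.5 rule, through causality, and the exception to it, so the overlap is narrower than the SAE definition alone suggests.

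**Conclusion.** The point holds as an internal inconsistency. In the extension, a confirmed hepatic event judged related under three of the four criteria in 5.6.8.1 falls under two rules that differ in default, test and decision maker whenever the harm exception does not apply. Separately, 6.4 does not respect the permanent stop in the fourth criterion. The conclusion assumes that withdrawal means leaving the study, as 4.5 uses the word, and that no precedence rule exists outside the text available.

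Four stronger readings are not supported:

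- That every confirmed hepatic event may be restarted on the sponsor's judgement. The ALT-against-baseline criterion forbids restart, the ALAT-with-symptoms decision is joint, and for the first two criteria the sponsor acts in discussion with the investigator. Section 6.4 does not name the sponsor as decision maker.
- That a safety stop can be overridden. For the first two criteria the confirmed stop is itself mandatory; only later resumption is discretionary.
- That one event moves a rate by a calculable amount, using 12 to 18 boys as denominator. Those are the dose-escalation numbers. Continuing needs the agreement of patient or parents, investigator and sponsor (synopsis, duration of treatment), and the number who continue is not given.
- That a main tolerability result is at risk. Withdrawal for related SAEs is not among the safety parameters in 8.5.6.2 or the analyses in 8.5.5.4, and the incidence of related events and of SAEs is counted there whether or not the boy is withdrawn.

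**What to change.** Reconcile 4.5, 7.1.2, 5.6.8.1 and 6.4 so that one section governs a hepatic SAE judged related to study medication, with one decision maker and one standard, and have the other three refer to it. State how the harm exception and the benefit-risk assessment relate to each other. State also how 6.4 applies to a stop that 5.6.8.1 calls permanent. Which rule prevails is a clinical decision for the sponsor and investigators.

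The cost is amendment text and retraining of sites. No new data, visits or assessments are needed.

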### **4.5.1 Withdrawal during study period**

A clear, concise reason should be recorded in the CRF for any subject prematurely ending the study. In addition, all subjects discontinuing should have a final visit including physical examination, vital signs measurement, ECG, safety biochemistry and hematology lab, urinalysis, dystrophin antibodies sample, pharmacokinetic sampling, muscle biopsy (if not yet collected at the time points as described in Table 4 in Appendix 2), muscle function and muscle strength (including FVC/FEV1 assessment) measurement.

In case a complete final visit is not possible, at least all safety assessments should be performed. All study data from withdrawals should be retained.

### **4.5.2 Withdrawal during treatment beyond study period**

A clear, concise reason should be recorded in the CRF for any subject prematurely ending the study. In addition, all subjects being withdrawn from the study should have a final visit including the following assessments (depending on the timing of withdrawal)

- Withdrawal at any time: physical examination, vital signs, safety biochemistry and hematology lab, urinalysis (dipstick, quantitative, alpha-1-microglobulin), cystatin C, muscle function and muscle strength (including spirometry assessment) measurement.
- Withdrawal prior to visit 37: aPTT, complement factor C3, pharmacokinetic sampling, muscle biopsy, ECG, dystrophin antibodies sample.
- Withdrawal prior to visit 61: ECG, dystrophin antibodies sample.
- Withdrawal prior to visit 85: dystrophin antibodies sample.

In case a complete final visit is not possible, at least all safety assessments should be performed. All study data from withdrawals should be retained.

## **5 Study plan**

All equipment used for assessments of effect, safety and pharmacodynamic variables should be calibrated and maintained at least yearly. Documentation regarding the calibration and maintenance has to be available for review by the monitor.

### **5.1 Screening procedures**

#### **5.1.1 Informed consent procedure**

This study is conducted in male subjects between 5 and 16 years of age. As for the informed consent procedure a distinction is made between subjects of twelve years of age and older and subjects under twelve years of age.

##### Subjects under 12 years of age

Both the subject and his parents (if they are the legal guardians) or legal guardian will receive oral and written information concerning the study. The subject and his parents/legal guardian should be given adequate time to read the information leaflet and an opportunity to ask the investigator any questions.

Following the provision of subject information, written consent will be obtained from the subject's parents or legal guardian prior to any study-specific procedure. The subject is not to enter the study if his parents/legal guardian have/has not understood the written and verbal information provided and/or has not personally signed and dated the consent form. A copy of the subject information leaflet and the signed informed consent will be provided to the subject's parents/legal guardian and a copy will be retained by the investigator.

